### Secondary analysis

Presence of *Ureaplasma* spp. at baseline (i.e., before randomisation) will be added as an interaction term for the main analyses of parent reported wheezing at 1-year corrected age and for survival without development of moderate/severe neurodevelopmental disability at 2-year corrected age. Main effects and interactions will be reported, as well as the *p*-value for the interaction term. Subgroup-specific estimates (with accompanying 95% confidence intervals) for each outcome will also be derived from model estimates.

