**Fig. 1 Fig1:**
[figure not shown]
SPIRIT figure

Mortality:Total number of deaths occurring from birth to 1- and 2-years of corrected age will be reported as will those occurring (a) from birth to 36 weeks’ PMA (which will have been reported in the AZTEC trial), (b) 36 weeks to never discharged and (c) after discharge.

Respiratory:

The main outcome will be parent reported wheezing at 1 year of corrected age. The following outcomes will also be reported:Length of the initial neonatal stay in hospitalNumber of infants discharged home on domiciliary ambulatory oxygenLength of oxygen supplementation (including at home)Parent reported wheeze from discharge to 2 years of corrected ageNumber of respiratory hospital admissions up to 1 year and 2 years of corrected ageNumber of prescribed respiratory drugsSurvival (from birth) without parent reported wheeze at 1 year of and 2 years of corrected age

Neurodevelopmental:

The main outcome will be survival (from birth) without combined moderate/severe neurodevelopmental disability at 2 years of corrected age. The following outcomes will also be reported at 2 years of corrected age:Moderate/severe neurodevelopmental disabilityThe proportion of infants who develop moderate-severe neurodevelopmental impairment, defined as Parent Report of Children’s Abilities–Revised (PARCA-R) questionnaire score of < 44Overall motor score as well as fine and gross motors scoresOverall language scores as well as expressive and receptive language scoresOverall cognition score

Combined moderate/severe neurodevelopmental will be defined, as previously [28, 29] as any of the following:Moderate or severe visual impairment (reduced vision uncorrected with aids, blindness in one eye with good vision in the contralateral eye or blindness or light perception only)Moderate or severe hearing impairment (hearing loss corrected with aids, some hearing loss uncorrected by aids, or deafness)Moderate or severe gross motor impairment (inability to walk or sit independently)Moderate or severe cognitive impairment will be defined using PARCA-R or by using clinical data if PARCA-R scores are missing. Total PARCA-R scores of less than 44 (range, 0 to 158, with lower scores indicating greater impairment) will be used to identify children with moderate or severe developmental impairment

Growth:Weight, height and head circumference will be reported at 1 and 2 years of corrected age after adjusting for sex and gestation

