#### Statistical analysis

A statistical analysis plan will be developed prior to the end of the study. Baseline descriptors will be given. Data analyses will be conducted to identify any differences in the respiratory, neurodevelopmental, and growth outcomes, as well as hospital admissions between the placebo and the treatment group using two-by-two tables and chi-square testing. We shall consider *p* < 0.05 as statistically significant and report 95% confidence intervals. We shall also model the data, as in our previous publications [6], to identify early life factors that may result in long-term respiratory/neurodevelopmental abnormalities including presence/absence of *Ureaplasma* spp. at baseline before intervention commenced in the neonatal period; and if the treatment effect is influenced by early life factors, e.g. gestation, sex, and use of mechanical ventilation. Initially, we shall report the univariable data with a view to including any relevant factors into a model (using linear or logistic regression as appropriate). Missing data will be included in the analysis as missing data.

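### The treatment comparison for both main outcomes is an unadjusted chi-square test, while the Ureaplasma interaction is to be added to a main model that the plan never names; one prespecified adjusted logistic model would serve both and gain some precision.

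*Protocol article*

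**What the plan says.** All references are to the protocol article.

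- **Statistical analysis, treatment comparison.** Differences in respiratory, neurodevelopmental and growth outcomes and in hospital admissions are to be sought "between the placebo and the treatment group using two-by-two tables and chi-square testing". No covariate is named.
- **Statistical analysis, modelling.** A further analysis has two stated aims: to identify early-life factors behind later abnormalities (baseline Ureaplasma among them), and to see "if the treatment effect is influenced by early life factors, e.g. gestation, sex, and use of mechanical ventilation". The route into the model is: "Initially, we shall report the univariable data with a view to including any relevant factors into a model", by linear or logistic regression.
- **Secondary analysis.** Baseline Ureaplasma "will be added as an interaction term for the main analyses of parent reported wheezing at 1-year corrected age", and likewise for survival without moderate or severe disability at 2 years. Main effects and an interaction p-value are promised, and subgroup-specific estimates "for each outcome will also be derived from model estimates".
- **Main objectives, Growth item.** Weight, height and head circumference "will be reported at 1 and 2 years of corrected age after adjusting for sex and gestation". Neither main outcome has a matching statement.
- **Background.** Low gestation is given as a factor linked to poorer neurodevelopmental outcome.

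The Statistical analysis section also says that a statistical analysis plan is still to be written. The Design section says that blinding continues.

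**The concern.** Two things do not sit well together. The only treatment comparison fixed for the main outcomes is a test on a two-by-two table, which has no terms, main effects or model estimates. The Secondary analysis section nevertheless speaks of adding a term to the main analyses. An analyst must decide whether the main analysis is the chi-square test or a regression that the plan does not name as main.

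The treatment comparison also makes no use of gestation and sex. Both are held, and the plan means to use both for growth. The only regression described for the main outcomes takes in factors after their univariable results have been seen. If that model came to supply the treatment estimate, its covariates would have been chosen from the data.

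At stake are some precision, protection against chance imbalance in measured predictors, and a single model from which both the main result and the Ureaplasma result come.

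**Working it through.** **Step 1. Reproduce the plan's own figure.** Inputs from Sample size, Table 1 and Table 2: 250 per group, 80% power, alpha 0.05 (two-tailed per the Discussion), wheeze 65% v 52.3%, survival without impairment 50% v 62.7%.

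n per arm = [1.96·√(2p̄(1−p̄)) + 0.8416·√(p₁(1−p₁)+p₂(1−p₂))]² / d², with d = 0.127. The continuity-corrected size is (n/4)·[1+√(1+4/(n·d))]².

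- Wheeze: p̄ = 0.5865. (1.365 + 0.581)² / 0.016129 gives 235; corrected, 251.
- Survival without impairment: p̄ = 0.5635. (1.375 + 0.585)² / 0.016129 gives 239; corrected, 254.

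The stated 250 is therefore the size for an unadjusted, continuity-corrected comparison of two proportions. Without the correction, power at 250 per arm is 82.4% and 81.9%. Sizing and chi-square test agree with each other.

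**Step 2. Set the analyses side by side.**

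| Analysis | Method stated | Covariates |
|---|---|---|
| Arm comparison | Two-by-two table, chi-square | None |
| Early-life factors and effect modifiers | Linear or logistic regression | Entered after univariable reporting |
| Ureaplasma interaction | Term added to the main analyses; model estimates | Base model not named |
| Growth | Listed under chi-square; reported as adjusted | Sex, gestation |

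The third row needs a model. The first row supplies none by name, and the second serves a different purpose.

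**Step 3. Relate the first and third rows.** Pearson's chi-square on a two-by-two table is the score test of a logistic regression containing arm alone. Adding Ureaplasma and arm × Ureaplasma to that regression gives a saturated model, whose subgroup estimates equal those from separate two-by-two tables. The interaction is thus an extension of an unadjusted main model, once that model is named.

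**Step 4. Size the gain from adjustment.** The protocol gives no strength for any baseline predictor, so strength is assumed. The simulation used 250 per arm and 4,000 runs per scenario. A single normal baseline score had a log-odds slope of 0, 0.4, 0.8 or 1.2 per SD, and intercepts were set so that the arm rates match Tables 1 and 2. The comparison is the uncorrected chi-square against the test of arm in a logistic regression on arm and score.

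| Score AUC (assumed) | Wheeze: chi-square → adjusted | Gain | Survival without impairment: chi-square → adjusted | Gain |
|---|---|---|---|---|
| 0.50 | 81.7% → 81.5% | −0.2 | 81.6% → 81.0% | −0.6 |
| 0.61 | 82.5% → 84.2% | 1.7 | 83.3% → 84.1% | 0.8 |
| 0.70 | 82.5% → 87.2% | 4.7 | 82.6% → 86.4% | 3.8 |
| 0.77 | 82.8% → 89.6% | 6.8 | 83.9% → 91.2% | 7.3 |

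The simulation error of one entry is about √(0.82×0.18/4000) = 0.6 points. Both tests ran on the same simulated data. The first row is read as no gain.

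**Step 5. Rough cross-check.** By the linear-model approximation, covariates explaining a share R² of outcome variance (assumed 5% to 15%) are worth 500/(1−R²) − 500 = 26 to 88 infants. The detectable difference becomes 12.7×√(1−R²) = 12.4 to 11.7 points.

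**The case against.** The strongest reply is that the plan is workable as it stands. The Statistical analysis section does foresee logistic regression, names baseline Ureaplasma and asks about effect modification. The Secondary analysis section speaks of model estimates, so a fair reader would fit the interaction in a logistic model. By Step 3, that model is a natural extension of the chi-square test. This stands. A reader might infer that the interaction cannot be fitted, or that the main and subgroup results are incompatible; the text supports neither.

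Second, an unadjusted chi-square test in a randomised comparison is valid, and the sample size was built for it. This also stands. The cost is efficiency, and type I error is not affected.

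Third, covariate lists belong in the analysis plan that is still to come. That would answer a complaint about missing detail. Here the protocol states a method for the treatment comparison, and then refers to its main analyses as if they were a model. A later plan has to depart from one of the two sections.

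Fourth, the univariable step belongs to an exploratory model that is not said to produce the treatment estimate. That is correct, so no charge of selective reporting follows. It is a reason to state the separation outright.

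**Conclusion.** The point holds as a matter of efficiency and coherence. The main comparison is valid but unadjusted, the interaction is attached to a main model that is not named, and a better method is available from data already held. The gain is about 0 to 7 points of power at 250 per arm. It depends entirely on the assumed strength of the baseline score (AUC 0.50 to 0.77), and is nil if gestation and sex predict little. The document links low gestation to neurodevelopment but gives no strength for it, and no figure for gestation or sex as predictors of wheeze.

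Three further readings are tempting and are not supported:

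- **Twins and triplets are wrongly treated as independent.** The document does not mention multiples, their share or how they were allocated, so neither the size nor the direction of any effect can be shown.
- **Known stratification factors are left out.** The Randomisation section only refers to the parent trial's publication. Nothing shown says whether randomisation was stratified.
- **Adjustment would repair the expected loss of 25 to 30% of survivors' outcome data.** That is a missing-data question. Adjusting for gestation and sex does not restore randomisation, and nothing shown says that response differs by arm.

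**What to change.** Amend the Statistical analysis and Secondary analysis sections, or settle it in the analysis plan before unblinding:

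1. Make the main analysis of each main outcome a logistic regression on allocated arm with prespecified baseline covariates: gestation, sex and, if the AZTEC randomisation was stratified, its stratification factors.
2. Report the standardised (marginal) risk difference and the odds ratio, each with a 95% confidence interval. The risk difference matches the percentage-point scale of the sample-size tables.
3. Fit the Ureaplasma main effect and the arm × Ureaplasma interaction as an extension of that same model, and take the subgroup estimates from it.
4. Keep the chi-square result as a supporting unadjusted analysis.
5. State that univariable screening does not determine the covariates of the treatment comparison. The exploratory modelling of early-life factors can stay as a separate analysis.

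The cost is wording, with no new data and no change to the sample size. The small downside is that the main estimate becomes model-based; showing the unadjusted result beside it lets readers judge how much that matters.

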## Discussion

The AZTEC trial’s main outcome is to assess if 10-day treatment with azithromycin, versus placebo improves survival without development of CLD. The AZTEC-FU study will follow-up AZTEC trial participants up 2 years corrected age, assessing mortality and important neonatal morbidities including respiratory, neurodevelopmental and growth outcomes. Important safety data will also be collected, including the incidence of potential consequences of early macrolide use, primarily pyloric stenosis.

The use of azithromycin for the prevention of CLD has been examined previously in smaller populations. A meta-analysis of six studies combining data for 469 infants reported potentially reduced rates CLD following neonatal azithromycin administration [32], but highlighted the need for an adequately powered study. A phase IIb study of 121 infants born at < 29 weeks’ gestation assessed *Ureaplasma*-free survival using an early 3-day course of 20mg/kg intravenous azithromycin. Whilst this treatment course proved effective in eradicating *Ureaplasma*, rates of CLD were not significantly different between the groups [33]. When this cohort was followed up at 2 years corrected age, there were no significant differences reported for respiratory or neurological outcomes between the treated and placebo groups, with comparable rates of cough, wheezing, hospitalisation, respiratory medication use and Bayley-III/neurodevelopment questionnaire scores between the two groups [34]. The longer, 10-day course of azithromycin being studied in AZTEC not only provides an antimicrobial effect against *Ureaplasma* but also provides an effective anti-inflammatory effect against the often reported early pulmonary inflammation [23, 35] that may confer additional benefit for the prevention of CLD. The AZTEC trial is not only sufficiently powered to address this question; it will also provide a larger cohort for follow-up and assessment of longer-term outcomes following early azithromycin use. Infants with CLD are known to be at increased risk of poorer respiratory health in the first 2 years of life, with increased parent-reported wheeze [36] and increased hospital admissions for respiratory diseases [4, 5], with a longer-term risk of decreased lung function [8]. If AZTEC proves effective at reducing rates of CLD for infants born < 30 weeks gestation, it will be important to follow these infants to see if there are longer-term benefits. For the AZTEC-FU study, we are aiming to recruit 500 infants which will enable detection of 12.7% improvement in parent reported wheeze and a similar difference for survival (from birth) without development of moderate/severe neurodevelopmental impairment between the azithromycin and placebo groups. Regardless of the success of the AZTEC trial, it is important to continue to follow-up these infants, as previous follow-up studies examining early neonatal interventions have demonstrated longer-term respiratory benefits, often without showing short-term benefits [37]. For example, despite early elective high frequency oscillatory ventilation not conferring a benefit on reducing rates of death or CLD in the neonatal period, infants treated with this ventilation modality had significantly improved lung function at 11–14 years of age [38].

Neurodevelopmental outcome following preterm birth is a key metric for parents and the neonatal community [39]. Preterm birth is inherently associated with increased risk of poorer neurodevelopment [11, 12], with a strong association, and shared risk factors, between CLD and functional and cognitive outcomes [15]. Human studies have shown that azithromycin is widely distributed in the brain tissue [40], with animal models suggesting that azithromycin may also confer neuroprotective benefits. However, human data for the neuroprotective efficacy of azithromycin is currently lacking. Whilst we postulate improved neurodevelopmental outcomes at 2-year corrected age for those infants treated with azithromycin, we shall also investigate if there are detrimental neurodevelopmental effects from the early use of early azithromycin by using two-tailed comparisons. With our anticipated 500 responses, we have estimated that we should be able to detect 12.7% differences for the main respiratory and neurodevelopmental outcomes at 1 and 2 years of corrected age respectively.

The AZTEC-FU studies are also monitoring survival up to 2 years of age, separately reporting deaths at important timepoints up to 2 years of corrected age. Growth is another important postnatal factor, with preterm infants having poorer inpatient growth velocities [41], and those with CLD were noted to have poorer growth once discharged home [16]. We are collecting anthropometric measurements, including weight, length and head circumference at discharge, and over the first 2 years of life from routine clinic appointments and health visitor assessments. If azithromycin proves effective at reducing rates of CLD, it will be important to assess whether that confers growth benefits following discharge home.

In summary, the AZTEC-FU studies are assessing the impact of a 10-day treatment course of early azithromycin in infants born < 30 weeks’ gestation on their mortality, respiratory morbidity, neurodevelopmental outcome and growth during the first 2 years of life. If azithromycin proves beneficial in improving survival without developing CLD in the neonatal period, the AZTEC-FU study should be sufficiently powered to demonstrate if improvements in respiratory symptoms, neurodevelopment outcome or growth occurs by 2 years of corrected age. Most importantly, the AZTEC-FU studies will ensure safety of the neonatal intervention and provide confidence in establishing azithromycin into routine care of preterm-born infants to improve survival without developing CLD.

## Ethics and dissemination

The current version of the AZTEC-FU Protocol is 7.0, dated 28 June 2022. The Wales Research Ethics Committee 3 (Ref 19/WA/0267) has granted ethics permissions and approved all amendments. The Health Research Authority (HRA) has granted NHS permissions. The study is registered on the NIHR portfolio. Cardiff University is the sponsor. The follow-up studies are an investigator-led project funded by Aspire Pharma Ltd. Results will be disseminated in peer-reviewed journals and via national and international conferences.

## Trial status

Protocol version 7.0 dated 28 June 22. Recruitment began in December 2019 and should complete in September 2025.

## Abbreviations

AZTEC: Azithromycin therapy for chronic lung disease of prematurity
AZTEC-FU: Azithromycin therapy for chronic lung disease of prematurity follow-up studies
CLD: Chronic lung disease of prematurity
PMA: Post menstrual age
COPD: Chronic obstructive pulmonary disease
PARCA-R: Parent Report of Children’s Abilities–Revised
NDAU: National Database Analyses Unit
QR: Quick response
